# Above-versus below-elbow casting for conservative treatment of distal radius fractures: a randomized controlled trial and study protocol

**DOI:** 10.1186/s12891-018-2007-9

**Published:** 2018-03-27

**Keywords:** Distal radius fracture, Conservative treatment, Treatment outcome, Randomized, Prospective

## Abstract

**Background:**

A variety of cast options are available for the non-surgical treatment of distal radius fractures (DRF) in adults. However, the literature is inconclusive regarding the need to immobilize the elbow joint after reduction in order to prevent rotation of the forearm in order to maintain the reduction of DRF. This study aimed to evaluate the best method of immobilization between above-elbow (AE) and below-elbow (BE) cast groups at the end of six-month follow-up.

**Methods:**

This is a randomized clinical trial with parallel groups and a blinded evaluator. There are two non-surgical interventions: AE and BE. Patients will be randomly assigned. A hundred twenty eight consecutive adult patients with acute (up to 7 days) displaced DRF of type A2, A3, C1, C2 or C3 by the Arbeitsgemeinschaft für Osteosynthesefragen (AO) classification will be included. The primary outcome will be the maintenance of reduction by evaluation of radiographic parameters and Disabilities of the Arm, Shoulder and Hand Questionnaire (DASH). Secondary outcomes include function measured by Patient Rated Wrist Evaluation (PRWE), pain measured by the Visual Analogue Scale (VAS), objective functional evaluation (goniometry and dynamometry) and rate of complications. Evaluations will be performed at 1, 2, 3, 4, 6, 8, 12 and 24 weeks. For the Student’s t-test, a difference of 10 points in DASH score, with 95% confidence interval, a statistical power of 95%, and 20% sampling error. We consider an extra 10% for balancing follow up losses results in 64 patients per group.

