## Background

Although distal radius fractures (DRF) are among the most frequent of the upper limb [1], the best method of treatment and outcome of these fractures has not yet been fully defined [2, 3]. Regarding non-surgical treatment, Cochrane review based on randomized controlled trials has concluded there are controversial in terms of the type of casting to be applied after the initial fracture reduction and there is no conclusive evidence of difference in outcome between different positions and methods of plaster and brace management for the common types of DRF [4–6].

Below-elbow (BE) splinting is easier to apply, is lower in cost, lighter, provides greater comfort, better function for daily life activities and less articular stiffness of the elbow [7–9]. Casts that include the elbow joint, which prevents the rotation of the forearm, may result in greater stability of the fracture and less risk of loss of reduction and need for re-reduction [10–12]. Other studies found similar results between immobilization methods in maintaining the initial fracture reduction [13, 14].

This study is based on the hypothesis that above-elbow (AE) splint immobilization in patients with DRF will present better results for loss of reduction and radiographic parameters, but more complication rate and worse functional outcomes when compared to below-elbow (BE) immobilization methods at the end of a six-month follow-up.

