### Primary outcomes

#### Radiographic parameters

Maintenance of reduction by evaluation wrist radiographs in PA and lateral x-rays at the following intervals: one, two, three, four, six, eight, twelve and twenty-four weeks after fracture reduction.

The radial height, radial inclination, volar tilt, ulnar variance, intra-articular step off or gap and carpal alignment will be used to determine maintenance of reduction at every follow-up visit. Measurements will be made on the radiographs with a marker, straight edge, and protractor by two researchers independently on different occasions.

We will consider maintenance of reduction if:loss of reduction ≤2 mm in radial heightloss of reduction ≤4 degrees in radial inclinationdorsal angulation ≤10^o^≤ 2 mm intra-articular step offpositive ulnar variance ≤3 mmany carpal malalignment.

The contralateral side is used as a reference.

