#### Patient-reported functional outcomes

Functional status will be evaluated by means of DASH questionnaire (validated for the Portuguese language) at the following intervals: two, six, eight, twelve and twenty-four weeks after fracture reduction [28]. The DASH was developed as an instrument for patients with upper-extremity injuries. The survey contains 30 questions related to the function of the hand, wrist, elbow, and shoulder based on the conditions to do certain activities in the past week, so the evaluations refer only after the beginning of the immobilization.

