#### Statistical methods

Descriptive data will be exposed as means or proportions followed by standard deviations or 95% confidence intervals. As a method to confirm the effectiveness of the randomization, baseline data will be compared in the two groups of comparison. To ensure the normal distribution of data, we will use visual analysis and Shapiro-wilk test.

For comparison between proportions, we will consider Pearson’s chi-square test. For continuous data, we will use Student T test. Intra-group comparison (1, 2, 3, 4, 6, 8, 12 and 24 weeks) will be analyzed by paired Student T test or Wilcoxon (if data is not normally distributed). We will consider as significant when alpha < 0,05. To analyze the occurrence of complication after treatment, we intend to perform survival analysis associated with Kaplan-Meier curves, if we find greater than 20% complication in any of the comparison groups. All statistical analysis will be performed following intention to treat principle. Statistical advisors will be blinded to the treatment groups as an effort to decrease bias.

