#### Sample size calculation

Based on data derived from one recent randomized clinical trial on the subject [32]. We considered as relevant differences on DASH scores (clinically relevant) when scores are greater than 10 points and standard deviation 15 points [33]. To detect this difference (Student T-test) and statistical power of 95% resulted in a 58 patient sample size per group. We considered an extra 10% for balancing follow up losses. Thus, our inclusion target will be 64 patients per group. We considered the test as bicaudal.

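### Two primary outcomes are each tested at 0.05 with no rule for combining them and no fixed visit, and the 95% power covers only one of them, a single DASH comparison

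*Protocol article*

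**What the plan says.** The abstract of the protocol article gives two primary outcomes: "The primary outcome will be the maintenance of reduction by evaluation of radiographic parameters and Disabilities of the Arm, Shoulder and Hand Questionnaire (DASH"). The body repeats this, with both outcomes under a plural heading, Primary outcomes.

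- **Maintenance of reduction** (Radiographic parameters): "The radial height, radial inclination, volar tilt, ulnar variance, intra-articular step off or gap and carpal alignment will be used to determine maintenance of reduction". It is assessed at eight visits: "one, two, three, four, six, eight, twelve and twenty-four weeks after fracture reduction".
- **DASH** (Patient-reported functional outcomes): assessed at five visits, "at the following intervals: two, six, eight, twelve and twenty-four weeks after fracture reduction".

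Statistical methods sets a single criterion: "We will consider as significant when alpha < 0,05". The Sample size calculation makes the test two-sided and rests on DASH alone, with a difference of 10 points and an SD of 15: "To detect this difference (Student T-test) and statistical power of 95% resulted in a 58 patient sample size per group". Ten per cent is added for losses, giving 64 per group. The abstract describes the same calculation as having "a statistical power of 95%, and 20% sampling error"; the second half of that phrase does not appear in the body.

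The Aim sets the comparison at six months. The Background hypothesis is that above-elbow immobilization "will present better results for loss of reduction and radiographic parameters, but more complication rate and worse functional outcomes".

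**The concern.** With two primary outcomes, the article needs to say what counts as success. It could be a significant result on either outcome, on both, or on one of them ranked first. None of these is stated, and the choice determines both the false-positive rate and the power.

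The gap matters more than usual here because the outcomes are expected to disagree. If the hypothesis is true, the radiographs favour the above-elbow cast and DASH favours the below-elbow cast. Each cast could then be called best on the strength of its own primary test, and the article gives no rule for choosing.

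The visit is also open. The aim points to week 24, but both outcomes are listed at every assessment. The Discussion presents DASH at 2 and 6 weeks as a comparison between the groups.

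Finally, the sample size says nothing about maintenance of reduction. The abstract's Discussion names that outcome first when it describes what the trial should settle, namely whether the elbow must be immobilized.

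**Working it through.** **Inputs from the article.** DASH difference 10, SD 15, two-sided alpha 0.05, power 95%, 58 per group plus 10%, giving 64; five DASH visits; eight radiographic visits. **Assumed, because the article gives none:** correlations between test statistics, and loss-of-reduction rates.

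**1. The article's own figure.** n per group = 2 × [(z for 0.05 two-sided + z for 95% power) × SD / difference]² = 2 × [(1.960 + 1.645) × 15/10]² = 58.5. An exact t-test needs 59.5. At 58 per group, t-test power is 94.5% (normal approximation 94.8%). Also 58 × 1.1 = 63.8, so 64. The stated size is therefore reproduced for one DASH comparison. For 80% power the t-test needs 36.3, so 37 per group. The design thus matches 95% power and not a 20% type II error.

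**2. Error rate if either outcome suffices, one time point.** With independent tests, 1 − 0.95² = 9.75%. With correlation 0.5 it is 9.1%, and with 0.9 it is 7.0%. The 9.75% is the ceiling.

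**3. Error rate if visits are also compared between groups.** These are simulated normal test statistics, each at two-sided 0.05.
- DASH at five visits: 18% at correlation 0.5, 15% at 0.7.
- All 5 + 8 = 13 outcome-visits, with one maintenance status per visit:

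| Correlation within outcome | Outcomes uncorrelated | Correlation 0.3 between outcomes |
|---|---|---|
| 0.5 | 39% | 37% |
| 0.7 | 31% | 30% |
| 0.9 | 21% | 20% |

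**4. Power if alpha is split.** At 0.025, 58 per group gives 90.5% for DASH (normal approximation 91.1%). Keeping 95% would take 70 per group by t-test (69.2 before rounding).

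**5. Power if both must succeed.** Each test stays at 0.05. Joint power is at most the smaller of the two powers, so at most 94.5%. As an illustration, if the outcomes were independent and maintenance had 80% power, joint power would be 0.945 × 0.80 = 75.6%.

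**6. What 58 per group offers for maintenance of reduction.** Normal approximation to the chi-square test. Power = Φ[(d − z × SE under no difference) / SE under the difference d], where z is 1.960 at 0.05 and 2.241 at 0.025. Detectable difference in percentage points:

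| Assumed loss rate, better arm | 80% power, 0.05 | 95% power, 0.05 | 80% power, 0.025 | 95% power, 0.025 |
|---|---|---|---|---|
| 10% | 20.8 | 27.9 | 23.4 | 30.6 |
| 20% | 24.1 | 31.3 | 26.7 | 33.9 |
| 30% | 25.5 | 32.6 | 28.2 | 35.1 |
| 40% | 25.8 | 32.4 | 28.3 | 34.8 |
| 50% | 25.0 | 31.1 | 27.3 | 33.2 |

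Smaller contrasts have little power at 0.05: 20% versus 30% gives 24%, and 30% versus 50% gives 60%.

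**The case against.** The strongest reply has four parts.

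- **The power statement is right for its test.** This stands. A reader might infer that the 95% is an error. It is not: 58 per group gives 94.5% for the DASH test described. The fault is that it covers one of two primaries.
- **The six radiographic parameters are not six tests.** This also stands. A reader might multiply six parameters by eight visits and conclude that dozens of primary tests are planned, with an error rate far above those shown here. The article uses the parameters as cut-offs for one status per visit and plans no separate between-group test of each.
- **The aim fixes six months, and the visit-by-visit testing in Statistical methods is within group.** This stands in part. The 20% to 39% range is therefore an upper reading under assumed correlations, not the trial's stated error rate. But the outcome text covers every visit, and the Discussion describes early DASH as a comparison between groups, so the primary visit is not settled.
- **Multiplicity rules usually sit in an analysis plan, which is not shown.** True of details. But the article itself fixes two primaries, a 0.05 threshold and a DASH-only sample size. A later alpha split would lower the DASH power printed here, and no analysis plan could turn 58 per group into a calculation for maintenance of reduction.

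It is also tempting to read "a statistical power of 95%, and 20% sampling error" as a contradiction in the design. That holds only if sampling error means type II error, and the sample size does not behave that way. It is unclear abstract wording with no effect on the design.

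**Conclusion.** The concern holds in this limited form. The missing decision rule leaves one of two properties unsupported, and they need not both fail. Under an either-outcome rule the family-wise error is up to 9.75% at one time point instead of 5%. Under a both-outcomes rule the error rate is sound, but joint power is unknown and capped at 94.5%.

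The two-test ceiling needs no assumption about correlation. The all-visit range does, and it also assumes that all 13 outcome-visits are compared between groups. The detectable differences for maintenance depend on assumed loss rates, which is why they are shown from 10% to 50%.

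Because the hypothesis expects the outcomes to point to opposite casts, the rule decides what the trial may conclude.

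**What to change.** 1. Name one time point for each primary outcome. Week 24 matches the stated aim; if the sponsor wants DASH during immobilization as a primary, it should say so and count it.
2. Define maintenance of reduction as a single composite status, and say whether it means the status at that visit or any loss up to it. Loss of reduction leads to an indication for surgery under Complications, so these are different endpoints.
3. Test the two primaries with Holm at overall two-sided 0.05, or state that both must succeed and in which direction each.
4. Make other visits and individual parameters secondary.
5. Under Holm, restate DASH power as about 90% at 58 evaluable per group (the first step, at 0.025).
6. State the detectable difference for maintenance at the alpha actually used, with the assumed loss rates.
7. Report both primaries together before calling either cast best.
8. Delete or clarify the sampling-error phrase in the abstract.

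The cost is wording in the protocol or analysis plan, ideally settled before unblinding. Under Holm the stated DASH power falls from 95% to about 90%. No extra patients are needed.

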**Discussion:**

Results from this study protocol will help to define the need for elbow immobilization in maintenance of reduction, as well as functional performance of below elbow cast versus above elbow cast immobilization during the immobilization period.

**Trial registration:**

NCT03126175 (http://clinicaltrials.gov). April 24, 2017.

## Background

Although distal radius fractures (DRF) are among the most frequent of the upper limb [1], the best method of treatment and outcome of these fractures has not yet been fully defined [2, 3]. Regarding non-surgical treatment, Cochrane review based on randomized controlled trials has concluded there are controversial in terms of the type of casting to be applied after the initial fracture reduction and there is no conclusive evidence of difference in outcome between different positions and methods of plaster and brace management for the common types of DRF [4–6].

Below-elbow (BE) splinting is easier to apply, is lower in cost, lighter, provides greater comfort, better function for daily life activities and less articular stiffness of the elbow [7–9]. Casts that include the elbow joint, which prevents the rotation of the forearm, may result in greater stability of the fracture and less risk of loss of reduction and need for re-reduction [10–12]. Other studies found similar results between immobilization methods in maintaining the initial fracture reduction [13, 14].

This study is based on the hypothesis that above-elbow (AE) splint immobilization in patients with DRF will present better results for loss of reduction and radiographic parameters, but more complication rate and worse functional outcomes when compared to below-elbow (BE) immobilization methods at the end of a six-month follow-up.

## Methods/design

### Aim

To determine the best method of immobilization in patients with distal radius fractures at the end of a six-months: below-elbow versus above-elbow cast.

### Design and setting

Randomized controlled trial developed at Federal University of São Paulo - UNIFESP and Hospital Municipal [name] Pires da Rocha - SP.

### Participant characteristics

Adults with growth plate closure, both genders, with unilateral and closed acute displaced DRF (up to 1 week), associated or not with the ulnar styloid fractures with no other fractures, which may be closed reduced and meet inclusion criteria (Fig. 1).

**Fig. 1 Fig1:**
[figure not shown]
Flowchart of patients included in this study

### Inclusion criteria

Displaced and reducible fractures classified by AO as type A2, A3, C1, C2 and C3 will be included if one of these conditions is present.Radial height – loss >2 mm [15–19].Radial Inclination - loss >4° [17, 20, 21].Dorsal angulation >10^o^ [5, 18, 20].Positive ulnar variance – loss >3 mm [19–21].Intra-articular step off or gap – >2 mm [5, 19, 22].Carpal malalignment [19, 23].

The contralateral side is used as a reference.

### Exclusion criteria

Patients presenting one or more of the following criteria will be excluded from this study:Open fractures, bilateral fracture or associated with tendon or neurovascular lesions.Associated carpal fractures.Marginal fractures or fractures from shearing mechanism.Fractures with palmar deviation (Smith’s fracture).Irreducible fractures (closed method).Prior history of a degenerative or traumatic disorder of the affected or contralateral wrist joint.Systemic diseases or traumatic lesions associated with fracture that restrict the application of methods or the evaluation of results.Cognitive deficit that does not allow the patient to understand the elements of the functional evaluation.Consent Form Refusal.

### Radiological measurements

The volar tilt, the radial inclination, the radial height, the ulnar variance and the intra-articular step off or gap were determined on posteroanterior (PA) and lateral (L) radiographs views obtained using a standardised procedure [24].

The standard method of obtaining a PA radiograph is with the shoulder in 90° of abduction, the elbow in 90° of flexion and the wrist in a neutral position. For the lateral view, the shoulder is adducted and the elbow is in 90° of flexion with the hand positioned in the same plane as the humerus [19].

The volar tilt, also called palmar tilt is measured on the lateral view and refers to the distance between a line through the dorsal and palmar boundary points of the radial joint surface and the perpendicular to the longitudinal axis of the radial shaft.

The radial inclination, also know as radial deviation is measured on the PA view and refers to the distance between a line through the radial and ulnar boundaries of the radial joint surface and the perpendicular to the longitudinal axis of the radial shaft.

The radial height, also called radial lenght is measured on the PA view and refers to the difference in axial direction of the radius between the distal tip of the radial styloid and the most distal aspect of the ulnar articular surface.

The ulnar variance, also called the radioulnar index is measured on the PA view and refers to the vertical distance between a line parallel to the medial corner of the articular surface of the radius and a line parallel to the most distal point of the articular surface of the ulnar head, both of which are perpendicular to the long axis of the radius.

The intra-articular step off or gap is measured on PA or lateral view and refers articular incongruity.

The carpal alignment is measured on lateral view. Two lines are drawn, one along the long axis of the capitate and other along the long axis of the radius. The lines do intersect within the carpus.

### Initial treatment

All the patients with a distal radius fracture who arrive at the emergency room will undergo a standard protocol with clinical and radiographic examination (bilateral x-rays of the wrist in PA and lateral views). After applying the inclusion and exclusion criteria, eligible individuals will be informed about the nature and purpose of the study, by reading the “Consent Form” and after signing it they will be included. On a pre-scheduled date (up to 7 days), the study participant will be referred to the main operating room to be anesthezied before closed reduction of the fracture under radioscopy control. The reducibility criteria will be evaluated and patients that have reducible fracture will be randomized and treated by one of the two methods of the study (Fig. 2). Patients that do not have closed reducible fracture will be excluded from the study and will receive surgical treatment (open reduction and internal fixation) on a date to be scheduled.

**Fig. 2 Fig2:**
[figure not shown]
Types of immobilization. Below-elbow cast (**a**). Above-elbow cast (**b**)

### Anesthesia

Intravenous anesthesia will be performed by aseptic technique. A simple bolus injection with Propofol (infusion rate 180 mcg.kg^− 1^.min^− 1^) in combination with opioid (fentanyl 5–10 mcg.kg^− 1^) adjusted to the individual needs of each patient and repeated as many times as necessary according to the anesthesiologist’s criteria [25, 26].

### Method for closed reduction and immobilization

The patient will be submitted to the closed reduction of the fracture through a traction and counter-traction technique. Materials needed for application of the two splinting techniques will be available in the operating room. Initially, all patients will receive a short radial splint that will be performed with a 20 cm wide gypsum cut to fit the thumb (Fig. 2a). The splint will be applied to the radial aspect of the wrist covering the volar and dorsal portion of the radius to the elbow. The splint will be moulded with three point fixation as described by Charnley [27]. The three points will be defined after a metal pointer will be placed beside the limb to identify the site of fracture by using the image intensification. Patients randomized to the above-elbow splint will receive a complementation of immobilization with a 15 cm width splint on the ulnar aspect of the forearm that begins at the middle of the forearm and extends into the armpit. The elbow will be immobilized at 90 degrees, and in a neutral position to block pronosupination (Fig. 2b). Cotton tubular mesh, cotton stripes and crepe bandage will be used in both bindings. Regardless of the immobilization adopted, all wrists will be positioned with slight flexion and ulnar deviation. Patients will be encouraged to actively move their fingers and the ipsilateral shoulder.

Patients with above-elbow immobilization will remain for 4 weeks with the splint followed by 2 weeks of below-elbow immobilization. The immobilization will be removed after 6 weeks.

